### Study design

2.1

The study will adopt a double-blinded crossover randomized controlled design involving two clinical centers in Italy. The whole intervention will consist of two treatment phases (sham vs. real multifocal stimulation) and multiple assessment phases (T1, T2, T3). One-week washout will be interleaved between the two treatment phases (see Figure 1).

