### Intervention

2.4

The intervention will consist of multifocal brain stimulation combined with cognitive training. In a cross-over design, 16 stimulation sessions (two sessions for week; freely scheduled from Monday to Friday on participants’ and institutional needs) will be delivered in two blocks (8 real and 8 sham stimulation sessions) for 10 weeks. The first and the last stimulation sessions of each block (namely sessions 1, 8, 9 and 16; Figure 1) will be preceded and followed by 5-min resting state EEG recordings with eyes-opened. Recruited participants will be randomly assigned to a “SHAM-REAL” stimulation group (G1) or a “REAL-SHAM” stimulation group (G2; Figure 1) by computer-generated random numbers; one investigator (FP) will manage generation of allocation sequence and participants’ assignment to the groups. The experimenters responsible for delivering the stimulation (LC) will be blind to the stimulation being delivered during each session. Throughout the study, all participants will undergo traditional cognitive stimulation therapy, embracing within each session paper-and-pencil and computerized activities during a face-to-face interaction with the therapist at the rehabilitation service. Activities will target memory, attention, and executive functions (24, 25); the level of difficulty will be tailored on the patients’ neuropsychological profile and progressively adjusted based on patients’ response to the treatment. Each session of cognitive training will last 40 min and will follow the brain stimulation session.

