### Sample size justification and statistics

2.8

The final sample size of 60 participants is estimated based on a sample size calculation on G*Power (v. 3.1.9.7) suggesting a sample size of at least 48 participants to compare the two groups along three-time points with an effect size = 0.25, power = 0.80, *ε* = 0.75, and a Bonferroni-adjusted *α* = 0.0125 (0.05/4 primary cognitive outcomes see below) and considering a dropout rate up to 30% from previous studies (37, 38).

Demographic data will be reported using descriptive statistics. Primary outcomes will be the measures of cognitive (MOCA, FAB, FCSRT, Stoop scores) and affective (GDS scores) functioning, while independence in daily living (ADL and IADL scores) and EEG parameters will be considered as secondary outcomes. Intention-To-Treat (ITT) analyses (39), which includes all randomized participants in the groups assigned, regardless of their adherence with the entry criteria, will be adopted. ITT analysis admits noncompliance and protocol deviations and gives an unbiased estimate of the intervention effect. Missing data will be dealt with by using a mixed-effect model approach which accommodates missing data under the missing-at-random assumption (40). To assess the effect of the intervention on multiple dependent variables simultaneously, repeated-measures analyses of variance (ANOVAs) will be conducted on the primary outcomes and secondary outcomes separately with the factors Group (G1 vs. G2) and Time (T1-T3). Moreover, multiple regression models will be used to identify the factors associated with the treatment outcome, considering gender, age, education, CRS scores, and EEG power spectrum at baseline as predictors and post intervention measures of general cognitive functioning (MOCA and FAB) and functional independence measures as criteria.

To assess possible sequence or carryover effects, an exploratory comparison of treatment effects between the two randomization arms (sham first over real vs. real first over sham) will be performed.

Statistical analysis will be performed using IBM® SPSS® Advanced Statistics and R package (R Foundation). Statistical significance will be set at *p* < 0.05.

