However, as discussed by recent studies in the field of closed-loop and brain state-dependent stimulation (50, 51), implementing truly individualized closed-loop therapeutic systems capable of reliably extracting complex brain states in real-time and identifying suitable biomarkers is currently a proof of concept and faces significant engineering and neurophysiological challenges. Moreover, strong and replicable evidence regarding the safe and effective modulation of cognitive and affective functions would be needed in healthy samples before these advanced prototypical approaches can be widely applied for rehabilitative purposes. The understanding of how our intervention affects brain oscillations seems to be a necessary step towards informing the development of future, potentially more personalized and state-dependent stimulation approaches in clinical populations.

It is possible that certain issues may impede the completion of the study protocol. A preliminary issue pertains to the participation of patients in the study, as some may prematurely withdraw from the study, thus failing to complete the full intervention program. This will be addressed through the provision of a comprehensive presentation of the study procedures and features to patients and their family members prior inclusion in the study; moreover, we will recruit a percentage of 25–30% more than the minimum sample size to ensure sufficient power to the analyses. A second issue concerns the multicenter nature of the study, which may necessitate the use of procedures that differ slightly from those employed at the other participating institution. To ensure the reliability and standardization of data acquisition and analysis processes, the experimenters involved in data acquisition at each study site will receive training and participate in regular peer-to-peer and supervision meetings. Lastly, a prompt evaluation of contraindications to brain stimulation by a physician with expertise in this field will prevent adverse effects and premature cessation of the intervention.

In conclusion, the study protocol described here responds to the new challenges posed by the ageing population, by devising an integrated rehabilitation treatment and by assessing multiple factors associated with its efficacy. Addressing these emerging issues will contribute to tackle a fundamental social problem, and to enhance quality of life of patients and their caregivers (52).

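### The models in section 2.8 omit centre, which could produce spurious predictors in the outcome regression and may cost the real-versus-sham comparison a little precision

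*Protocol article*

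**What the plan says.** Section 2.1 describes a "double-blinded crossover randomized controlled design involving two clinical centers in Italy". Section 2.2 names them: a hospital in Naples and the neuropsychological testing service of a university department in Caserta.

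The Discussion lists the multicentre setting among the issues that might impede the study, because it "may necessitate the use of procedures that differ slightly from those employed at the other participating institution". The stated remedy is that the experimenters who acquire data at each site "will receive training and participate in regular peer-to-peer and supervision meetings". No handling in the analysis is mentioned.

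Section 2.8 states two sets of models:
- Repeated-measures ANOVAs on the primary and secondary outcomes, "separately with the factors Group (G1 vs. G2) and Time (T1-T3").
- Multiple regressions "considering gender, age, education, CRS scores, and EEG power spectrum at baseline as predictors". The criteria are post-intervention MOCA and FAB and the functional independence measures.

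Centre is in neither list. Section 2.8 also mentions a mixed-effect approach for missing data but does not give its terms.

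**The concern.** A hospital and a university testing service may well draw different patients and may test or record them somewhat differently. The two analyses are exposed to this in different ways.

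The regression models levels after treatment, with no baseline score of the criterion among the listed predictors. A site that has, say, better-educated patients and also higher scores (through case mix or scoring) would make education look like a predictor of outcome even if it has no effect within either site. This analysis carries one of the trial's stated aims: the abstract, the hypotheses at the end of the Background and the Discussion all rely on it to show which patients suit the intervention.

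The real-versus-sham comparison is made within participants, so it is exposed only if participants at the two sites change differently over time.

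**Working it through.** **1. The plan's own sample size.** Inputs from section 2.8: "effect size = 0.25, power = 0.80", ε = 0.75, α = "0.0125 (0.05/4 primary cognitive outcomes see below"), two groups, three time points. The correlation between time points is not stated; 0.5 is assumed. For the Group-by-Time interaction:
- λ = f²·N·m·ε/(1 − ρ) = 0.0625 × 48 × 3 × 0.75/0.5 = 13.5
- df1 = (2 − 1)(3 − 1) × 0.75 = 1.5
- df2 = (48 − 2)(3 − 1) × 0.75 = 69

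The power is 0.816, and 48 is the smallest even N that reaches 0.80, so the stated figure is reproduced. At N = 60 the power is 0.910. The required N depends on the assumed correlation: 66 at 0.3, 38 at 0.6 and 30 at 0.7.

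**2. Regression.** Assume two equal centres, unit SD within centre and no true predictor effect. Centre shifts the predictor by *a* SD and the score by *b* SD. The variance of a 50:50 indicator is 0.25, so the slope without centre in the model is

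0.25ab/(1 + 0.25a²).

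For a = b = 0.5 this is 0.0625/1.0625 = 0.059. For a = 0.8, b = 0.5 it is 0.10/1.16 = 0.086. For a = b = 0.8 it is 0.16/1.16 = 0.138. A simulation with n = 60, one predictor and 6,000 runs per row gave these false-positive rates at a nominal 5%:

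| Shift in predictor / score (SD) | Mean slope, no centre | False positives, no centre | False positives, centre in model |
|---|---|---|---|
| 0 / 0.5 | 0.00 | 4.6% | 4.7% |
| 0.5 / 0 | 0.00 | 5.3% | 5.4% |
| 0.5 / 0.5 | 0.06 | 7.5% | 5.5% |
| 0.8 / 0.5 | 0.09 | 10.2% | 4.7% |
| 0.8 / 0.8 | 0.14 | 19.2% | 5.1% |

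The standard error of such a slope is roughly 1/√60 = 0.13, so the bias is about half a standard error at 0.5 SD and about one at 0.8 SD. It arises only when centre is related to both predictor and score.

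**3. Real versus sham, constant centre difference.** A constant added to T1, T2 and T3 for everyone at one site drops out of T2 − T1 and T3 − T2, and so out of the Group-by-Time interaction. Simulation agrees: the SD of that contrast was 0.444 with no centre effect and 0.450 with a 1 SD effect, a difference within simulation error. The effect falls on the Group main effect (SD 0.213 rising to 0.252), which compares sequences and not real with sham.

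**4. Real versus sham, centre-specific change.** Let the sites differ by *g* SDs of within-person change, with equal centres. As an approximation, residual variance is multiplied by 1 + 0.25g², and f becomes 0.25/√(1 + 0.25g²). For g = 0.5, f = 0.25/√1.0625 = 0.2425.

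| g | Power at N = 48 | Power at N = 60 |
|---|---|---|
| 0 | 0.816 | 0.910 |
| 0.25 | 0.809 | 0.905 |
| 0.5 | 0.787 | 0.889 |
| 0.8 | 0.741 | 0.854 |
| 1.0 | 0.701 | 0.821 |

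**5. Price of including centre.** With centre and centre-by-time in the model, df2 = (48 − 3) × 2 × 0.75 = 67.5, a loss of 1.5. Power is 0.815 instead of 0.816 at N = 48, and stays at 0.910 at N = 60.

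**The case against.** The strongest reply is that nothing in the article shows a centre difference of any size. The Discussion presents it as a possibility, calls it slight and pairs it with a remedy. Every shift used above is assumed, and the regression looks for associated factors; it is not the test of efficacy. Covariates beyond the design factors are often left to the analysis plan. All of this stands as a limit on the size of the point. It does not remove it: section 2.8 names its factors and predictors one by one, and centre is missing although the article itself raises site differences as an issue.

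Four stronger readings are tempting and are not supported:

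- *That the protocol expects its sites to differ.* It says only that they may, slightly. Nor does it show that therapy is delivered differently: section 2.2 calls the sites recruitment centres, section 2.4 places therapy at a single rehabilitation service, and the Discussion speaks of data acquisition at each site.
- *That any testing or scoring difference disturbs real versus sham.* A constant difference cancels, as shown in step 3.
- *That chance imbalance of the sequences within centre shifts the treatment estimate on top of inflating its error.* These are the same variance. Suppose simple randomisation of 30 + 30, a retest correlation of 0.7 and a difference in gain of 0.5 score SD. The standard error without a centre difference is √0.6/√60 = 0.10. The SD of the difference in centre share is 0.131, so the shift has SD 0.131 × 0.5/2 = 0.033. Then √(0.10² + 0.033²) = 0.105, about 5% more. The variance route gives the same: √(0.6625/0.6) = 1.05. This is chance variation, not bias.
- *That the allocation ignores centre.* Section 2.4 says only that groups are assigned "by computer-generated random numbers". That neither describes nor excludes stratification, a detail a condensed article may leave to the full protocol.

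**Conclusion.** The point holds as a modest, conditional defect of the stated models. Its core is the regression. If centre shifts both a predictor and the outcome level by 0.5 SD, the slope is biased by about 0.06 and the false-positive rate for that predictor is about 7.5%; at 0.8 SD for both, about 0.14 and 19%. With centre in the model the rate returns to about 5%. These figures assume equal centres, n = 60 and a single predictor; with several predictors the bias would be shared among them in a way the article does not allow one to compute.

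The real-versus-sham comparison remains valid. The only cost is precision, and only if change over time differs by centre: 0.816 − 0.787, about 3 power points, at N = 48 for a difference of 0.5 SD of within-person change. At the 60 completers of section 2.2, power in that case is still 0.889, above the planned 0.80.

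**What to change.** In section 2.8, add centre to the regression predictors, and add centre and centre-by-time to the Group-by-Time models of the primary and secondary outcomes.

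Centre is already known for every participant, so no data, visits or patients are added. The cost is one residual degree of freedom in each regression. In each ANOVA it is one between-participant and two within-participant degrees of freedom (1.5 after the ε correction), with the negligible power change shown in step 5. One or two sentences in section 2.8 are enough.

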Several systematic reviews and meta-analyses, however, have not provided conclusive data about effectiveness of NIBS delivered alone or combined with cognitive treatment on dementia and MCI. Teselink et al. (7) have found NIBS to significantly improve global cognition and affective symptoms relative to sham stimulation in patients with Alzheimer’s Disease (AD) and MCI. Subgroup analyses showed that these effects were mainly restricted to TMS and to patients with AD, while limited evidence was available for tDCS and MCI. Similar results were obtained by Simko et al. (8) who argued that TMS over the dorsolateral prefrontal cortex seemed to be effective in enhancing cognition in AD, whereas no clear effect was observed for MCI. In both studies no support was offered for combined cognitive stimulation therapy with NIBS intervention. A lack of relevant effects of tDCS in MCI was also confirmed by Saleh et al. (9), who called for implementation of neurophysiological methods to assess the possible brain mechanisms associated with the treatment and to identify possible markers of effective response to stimulation thus reducing variability of stimulation effects (10). These conclusions contrast with a recent systematic review and metanalysis by Yang et al. (11), according to which TMS in AD showed the best outcomes in improving global cognition, but relevant effects can be exerted by tDCS in AD and MCI as well. Crucially, Yang et al. supported a beneficial effect of NIBS combined with cognitive therapy.

Inconsistencies among the research reports could be ascribed to several factors including use of different methods to assess cognitive functions; moreover, evidence about effectiveness of tDCS in MCI is limited by the small number of studies targeting this issue, whereas more data are available on use of TMS in AD.

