To achieve these purposes the present study protocol will adopt a double-blinded sham-controlled crossover experimental design in patients with MCI and early stages of dementia, combining brain stimulation and electrophysiological recording. The primary outcomes will be global cognitive functioning, anterograde verbal episodic memory and executive functions as well as affective symptoms. Secondary outcomes will be the level of functional independence in daily living and electrophysiological measures. Based on the available literature we expected to observe an effect of brain stimulation on cognitive and affective functions (7, 11). Moreover, we expect the use of EEG recording being able to provide findings useful to distinguish good and bad responders to the treatment based on individual analysis (9, 10). Finally, we hypothesize that demographic factors can modulate the possible outcomes, thus contributing to identify the patients most suitable for such intervention (3, 7).

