### Participants

2.2

The recruitment centers for the study will be “Alma Mater Camaldoli Hospital” (Naples) and the Neuropsychological Testing Service of the Department of Psychology of University of Campania “Luigi Vanvitelli” (Caserta) in Italy. All participants consecutively admitted to the two centers will be screened for study participation. Data collection will be terminated when at least 60 participants will complete the whole intervention. Inclusion criteria are: (i) age between 55 and 85 years, and (ii) diagnosis of minor neurocognitive disorder, or major neurocognitive disorder with mild severity, according to Diagnostic and Statistical Manual of Mental Disorders [DSM-5; (20)] with a Clinical Dementia Rating Scale (CDR) of 0.05 or 1 (21), (iii) right handedness. The diagnosis will be made by expert neurologists and neuropsychologists. Exclusion criteria are: (i) brain events with an acute aetiology (stroke, traumatic brain injury, neoplastic ablation), (ii) psychiatric disorders (schizophrenia, psychosis, bipolar disorder) and assumption of psychotropic drugs, (iii) diagnosis of moderate or severe major neurocognitive disorders [DSM-5; (20)] with CDR scores equal or above 2 (21), (iv) any condition which might even hypothetically interfere with electrophysiological recording and neurostimulation (metallic implants in the brain, cochlear implant, pacemakers, epilepsy) (22, 23).

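### Disease stage is known for every patient at entry but used nowhere in the analysis, so the trial cannot say whether response differs by stage or separate its listed predictors from stage

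*Protocol article*

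**What the plan says.** Section 2.2 (Participants) admits patients with a "diagnosis of minor neurocognitive disorder, or major neurocognitive disorder with mild severity" and also requires a CDR rating, with consecutive admissions screened at two centres. Stage is therefore on record for everyone before randomisation. Section 2.4 describes allocation by computer-generated random numbers and mentions no stratification.

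Section 2.8 analyses primary and secondary outcomes by Group (the two sequences) and Time (T1 to T3). It then specifies multiple regressions "considering gender, age, education, CRS scores, and EEG power spectrum at baseline as predictors". The outcomes of those regressions are the scores after the intervention on MOCA, FAB and the functional independence scales. No baseline score, treatment term or stage variable is listed.

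The Background says of one meta-analysis that "these effects were mainly restricted to TMS and to patients with AD, while limited evidence was available for tDCS and MCI". It also cites a review with no clear effect in MCI, another with no relevant tDCS effect in MCI, and a more recent review that found tDCS effects in both AD and MCI. Its closing paragraph expects demographic factors to modulate outcome, "thus contributing to identify the patients most suitable for such intervention". The Discussion (section 3) looks forward to profiling likely responders.

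**The concern.** The protocol treats variable response as a question to be explained and picks candidate modifiers from earlier work. One meta-analysis is its source for two of them, age and diagnosis. Age enters the predictor list; diagnosis does not, and no reason is given.

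Two things are at stake.

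- **Interpretation of the overall result.** A null pooled result could conceal an effect confined to one stage. A positive one would be stated for MCI and early dementia alike when it might come mainly from one of them.
- **Interpretation of the predictors.** The regression outcomes are levels of cognition and function, which is what separates the two stages. Any listed predictor that differs between stages will be associated with those levels even if it has nothing to do with response to stimulation. Patients could then be selected on a characteristic that only marks stage.

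**Working it through.** **1. The text set side by side.** Stage is recorded at entry (2.2), is not a stratifier (2.4), and is neither a factor nor a predictor (2.8). The Discussion itself links stage to the regression variables: it describes people with MCI as often still of working age, and places loss of function from early dementia onward. So by the protocol's own account stage is related to a listed predictor (age) and to a listed outcome (functional independence). Links of stage with education, reserve and EEG power are plausible but not documented.

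**2. The plan's own sample size.** Inputs from 2.8: two groups "along three-time points with an effect size = 0.25, power = 0.80", epsilon as in "0.75, and a Bonferroni-adjusted", and alpha "0.0125 (0.05/4 primary cognitive outcomes see below". The figure is "estimated based on a sample size calculation on G*Power", but no correlation among repeated measures is given. I assume rho = 0.5 and show the range. For the within-between interaction, with k = 2 groups and m = 3 times:

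- lambda = f² × N × m × eps / (1 − rho) = 0.0625 × 48 × 3 × 0.75 / 0.5 = 13.5
- df1 = (k − 1)(m − 1) × eps = 1.5; df2 = (N − k)(m − 1) × eps = 69
- power = 0.816

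The stated 48 is reproduced. With rho = 0.3 the requirement is 66; with rho = 0.7 it is 30. This calculation concerns the pooled sample and makes no allowance for a comparison between stages.

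**3. What a stage comparison could show.** Take each patient's difference between the end-of-period scores under real and sham. Its SD is √(2(1 − rho)) outcome SDs, which is 1 when rho = 0.5. The standard error of the difference between stages is √(1/n1 + 1/n2), with N − 4 degrees of freedom (sequence by stage). The document gives no expected case mix, so the splits are assumptions.

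| N | Split | Power for 0.5 SD, alpha 0.05 | Same, alpha 0.0125 | Difference detectable with 80% power, alpha 0.05 |
|---|---|---|---|---|
| 60 | 50/50 | 48% | 27% | 0.74 SD |
| 60 | 70/30 | 42% | 22% | 0.80 SD |
| 60 | 80/20 | 33% | 16% | 0.92 SD |
| 48 | 50/50 | 40% | 20% | 0.83 SD |
| 48 | 80/20 | 27% | 12% | 1.03 SD |

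The detectable difference scales with √(2(1 − rho)). For N = 60 split evenly it is 0.74 × √1.4 = 0.88 SD at rho = 0.3 and 0.74 × √0.6 = 0.57 SD at rho = 0.7.

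Within a single stage, Group-by-Time power at f = 0.25 and alpha 0.0125 (rho = 0.5) is 55% for n = 30 and 16% for n = 12. A 95% interval for the real-minus-sham effect in one stage has half-width of about 1.96/√30 = 0.36 SD for n = 30 and 1.96/√12 = 0.57 SD for n = 12. These use the normal approximation and are slightly too narrow.

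**4. What the pooled effect means.** Purely as illustration, suppose the effect is 1 unit in dementia and 0 in MCI. The pooled effect then equals the dementia share: 0.7, 0.5 or 0.3 when MCI makes up 30%, 50% or 70%. This shows dependence on case mix; it does not estimate anything in this trial.

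**The case against.** Several stronger readings are tempting, and the document does not support them.

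- **A reader might infer that the protocol's own evidence shows a different benefit in the two stages.** It does not. The Background calls the reviews inconclusive, its AD/MCI contrast rests largely on TMS, and one cited review reports tDCS effects in both groups. The cited contrast is also AD versus MCI, whereas this trial enrols minor versus mild major neurocognitive disorder without requiring AD. What stands is that the question is open.
- **A reader might infer that the trial cannot identify suitable patients at all.** The Background ties that aim to demographic factors and EEG, and both are analysed. Diagnosis is not the only modifier it names: age is cited from the same meta-analysis. The gap is one candidate modifier, and the inability to separate the others from it.
- **A reader might infer that pooling biases the treatment effect.** Each patient receives both real and sham, so the within-patient contrast is not distorted by mixing stages.

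It can also be said that an exploratory subgroup by diagnosis is the kind of detail left to an analysis plan, and that its yield is low. The low yield is real and limits what can be claimed. But the article does name its predictors, and leaves stage out. Finally, simply adding stage to the regression as specified would mostly show that patients with dementia score lower. That objection is sound, and the fix has to meet it.

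**Conclusion.** The point holds in a limited form. As written, the analysis cannot say whether response to stimulation differs by stage. Associations of age, education, cognitive reserve or EEG power with post-intervention MOCA, FAB and function may reflect stage rather than response. The pooled real-versus-sham effect remains a valid average over whatever mix is admitted.

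This is an inexpensive improvement and not an error that invalidates the trial. Even when repaired, the stage comparison is exploratory: about 48% power for a 0.5 SD stage difference with N = 60 at alpha 0.05, given an even split and a correlation of 0.5, both assumed. Power falls to 33% with an 80/20 split. The size of any confounding of the listed predictors with stage cannot be computed from the document.

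**What to change.** In section 2.8:

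1. Define stage once (minor versus mild major neurocognitive disorder, or CDR level). If CDR is used, check the lower entry value as printed in section 2.2 first.
2. Add stage as a prespecified exploratory modifier of the within-patient real-minus-sham effect, through a stage-by-treatment term in the mixed model. Report that effect with a confidence interval in each stage, and report the case mix.
3. In the predictor regressions, use the real-minus-sham difference as the outcome, or at least adjust for the baseline score, and include stage as a covariate. The first option addresses response to stimulation; the second only removes much of the prognostic part.
4. Label stage-specific results exploratory, and limit statements about the most suitable patients to what the intervals allow.

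Stratifying randomisation by stage could be considered if enrolment permits.

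The cost is small: no new measurements, one covariate, one interaction, and a redefined or baseline-adjusted regression outcome. The drawback is that stage-specific estimates will be imprecise, especially if one stage dominates.
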